## Abstract

**Introduction:**

Epilepsy affects approximately 70 million people globally, with around 20−30% of these individuals experiencing drug-resistant epilepsy in which seizures remain uncontrolled despite prolonged treatment with anti-seizure medications (ASMs). Such refractory epilepsy significantly impairs quality of life, often necessitating surgical resection of the epileptic focus when ASMs fail. Accurate localization of the epileptic focus is crucial for successful surgery and typically requires invasive intracranial monitoring through subdural electrodes (SDE) or stereotactic electroencephalography (SEEG). Despite their effectiveness, the invasiveness of these methods poses significant risks. In response to these challenges, the EP-01 device has been developed to measure intracranial electroencephalogram (EEG) via the cerebral veins, offering a less invasive alternative. The Endovascular EEG Device Prospective Multicenter Single-arm clinical trial to confirm efficacy and safety performance on patients with Intractable Epilepsy (EPSILON IE) trial aims to evaluate the efficacy and safety of EP-01 in diagnosing the lateralization of epileptic foci in patients with focal epilepsy. The hypothesis is that EP-01, when equipped with multiple endovascular EEG electrodes, can accurately diagnose lateralization, reducing the need for more invasive procedures like SDE and SEEG.

**Methods and analysis:**

This multicenter, prospective, single-arm validation clinical trial is set to take place from March 2024 to August 2025, with follow-up extending to August 2026. The study will enroll 37 patients with refractory focal epilepsy across several Japanese medical institutions. Eligibility criteria include age 15–70 years and a vascular anatomy that allows the EP-01 to be guided into cerebral veins close to the epileptic focus. The EP-01 device will be inserted via the jugular veins, with electrodes positioned in target cerebral veins to record intracranial EEG data. The primary endpoint is the percentage agreement in lateralization diagnosis between EP-01 and conventional intracranial electrodes. Secondary endpoints include the diagnostic performance of EP-01, safety assessments, and seizure outcomes one year after resection surgery. Participants will undergo a screening period of 30 days, followed by the clinical trial period of up to two weeks, during which EP-01 will be inserted and monitored. A post-observation period of one week will follow device removal to assess potential adverse events. Data collection will involve EEG recordings, imaging studies, and safety evaluations, with results analyzed to determine the efficacy and safety of the device compared to traditional methods. This trial aims to provide critical data on the potential for EP-01 to serve as a less-invasive, effective alternative for diagnosing epileptic focus lateralization, potentially reducing the need for traditional invasive monitoring methods.

## 1. Introduction

### 1.1 Background and Rationale

Approximately 20–30% of patients with epilepsy worldwide are non-responsive to drug treatments and experience refractory seizures [1]. Refractory epilepsy is defined as a condition in which seizures remain uncontrolled for at least one year and interfere with daily life, even after at least two years of treatment with a single, primary anti-seizure medication (ASM) or two or more ASMs in combination with sufficient doses.

Approximately 70 million people around the world suffer from epilepsy [2], of whom approximately 20–30% have intractable epilepsy that remains unresponsive to pharmacotherapy [1]. Since ASMs fail to control seizures in these patients, surgical resection of the epileptic focus is considered the method of last resort. Currently, epileptic foci are first non-invasively identified using magnetic resonance imaging (MRI), computed tomography (CT), single-photon emission CT (SPECT), positron emission tomography (PET), and scalp electroencephalography (EEG) [3]. However, in numerous cases, determination of the resection area ultimately rests in invasive procedures such as placement of subdural electrodes (SDE) or stereotactic EEG (SEEG) before proceeding to focal resection [3,4]. Accurate estimation of the epileptic focus by invasive monitoring followed by successful resection surgery is key to increasing the chances of better seizure control in patients with intractable epilepsy.

Intracranial electrodes have therefore taken a lead role in determining the resection area. These electrodes are used for estimating the potential epilepsy focus and functional mapping [4,5]. The two types of intracranial electrode placement procedures are SDE and SEEG [3,4]. SDE covers the brain surface “as a plane” and implants electrodes subdurally by craniotomy. SDE is more invasive than SEEG, but allows the performance of functional mapping. By virtue of its reduced invasiveness, SEEG becomes more applicable in re-operative cases where SDE placement is difficult or where electrode placement in both hemispheres is desirable to determine the lateralization of the epileptic focus [3,4]. These intracranial electrodes are sometimes used alone in SDE or SEEG, and sometimes are used in combination, and are considered the gold standard for identifying the epileptic focus to decide the extent of resection [1]. Even though these procedures are invasive, false lateralization from scalp EEG that differs from intracranial electrodes can result in failed surgical isolation of the focus [6], so appropriate lateralization diagnosis by detecting signals directly from close to the epileptic focus in the brain parenchyma is very important.

To avoid signal attenuation by the skull and scalp, and to reduce the invasiveness of obtaining intracranial EEG compared to SDE and SEEG, we have considered the cerebral vasculature as a site from which to record intracranial EEG. We are developing EP-01 to measure intracranial EEG from within the cerebral veins by approaching from inside the blood vessels. The two main objectives of SDE electrodes are “intracranial EEG measurement” and “functional mapping”, but EP-01 is currently monopolar, making functional mapping impractical. However, we believe that the objective of “intracranial EEG measurement“by lateralization diagnosis of the epileptogenic zone can be achieved with endovascular EEG.

Mesial temporal lobe epilepsy is particularly effective for lateralization diagnosis because once lateralization is determined, amygdalohippocampectomy is performed on the determined side, so more precise identification of the resection area is unnecessary. Among focal resection procedures, amygdalohippocampectomy is known to be highly effective, with over 90% of patients successfully treated in terms of seizure control [7,8]. However, as mentioned above, accuracy in preoperative focal diagnosis is extremely important when performing other resection surgeries, since inaccurate preoperative focus diagnosis or lateralization will render the surgery ineffective. Intracranial EEG recording is therefore regarded as one of the most accurate methods of focal diagnosis since ictal EEG changes can be directly recorded from the site of seizure onset [9].

Since the 1960s, lateralization diagnosis has been performed using SEEG, and lateralization can be diagnosed even with a small number of electrodes. We therefore believe that lateralization diagnosis is also possible with EP-01. In addition, a case report in which a wire-like endovascular EEG electrode was placed in the cerebral artery showed that simultaneous placement of intracranial electrodes and endovascular EEG electrodes in a patient with temporal lobe epilepsy yielded similar epileptic spikes from both [10]. This endovascular EEG measurement was performed with only one electrode, but measurement from a single location is suboptimal for determining lateralization. Insertion of multiple electrodes into both cerebral hemispheres is thus needed to improve endovascular EEG.

### 1.2 Objectives and hypothesis

To assess the efficacy and safety of cerebral endovascular EEG for determining epileptic focus laterality in focal epilepsy, based on the hypothesis that simultaneous placement of multiple endovascular EEG electrodes in both hemispheres enables accurate lateralization.

### 1.3 Trial design

This multicenter, prospective, single-arm, validation clinical trial will be conducted on the study device from March 2024 to August 2025. The follow-up period for seizure evaluation will extend to August 2026. Evaluations of EP-01insertion performance will be determined by a Central Evaluation Committee comprising expert clinicians.

Essentially, the screening period is set at 30 days and the investigational testing period after insertion is a maximum of 2 weeks to facilitate testing and provide sufficient time for non-provoked spontaneous seizures to occur. The post-observation period (1 week) is judged as sufficient for monitoring potential adverse events associated with endovascular and intracranial implantation of electrodes. A summary of the processes for enrollment, conduct of the clinical trial, surgical treatment, and follow-up is shown in the Figure (Fig 1).

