**Fig 1 pone.0332387.g001:**
[figure not shown]
Study schedule of EPSILON IE. Essentially, the screening period is set at 30 days and the investigational testing period after insertion is a maximum of 2 weeks to facilitate testing and provide sufficient time for non-provoked spontaneous seizures to occur. The post-observation period (1 week) is judged as sufficient for monitoring potential adverse events associated with endovascular and intracranial implantation of electrodes. *Not required if epileptic seizures occur within one week of placement of the test device. ** EP-01 will be left in place until the onset of epileptic seizures or for a maximum of 14 days (plus 3 days). ***If the trial is to be stopped during the clinical trial inspection period, the tests specified at the time of removal of the EP-01 will be carried out as much as possible depending on the subject’s condition, the EP-01 will be removed, and the trial will move to the post-observation period. Suppose the trial is to be stopped during the post-observation period. In that case, the tests specified one week after removal of the test device will be carried out as much as possible depending on the subject’s condition, and the trial will then end. **** Only subjects who underwent epilepsy resection were included. ***** If the measurement is conducted within 90 days before obtaining consent, there is no need to remeasure, and data from before consent was obtained will be collected. ****** When only EP-01 or both EP-01 and intracranial electrodes are indwelled, EEG data from EP-01 and intracranial electrodes will be recorded under video surveillance. EEG data during eyes opening and closing (the investigator, etc. will decide the timing of EEG data acquisition during eyes opening and closing) and EEG data during epileptic seizures will be submitted to the Central Evaluation Committee.

This protocol has been described in accordance with the SPRIT checklist (Standard Protocol Items: Recommendations for Interventional Trials [11].

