**Secondary endpoints.**

(1)Diagnostic performance of the EP-01 alone, without reliance on intracranial electrodes, for the diagnosis of lateralization of the epileptic focus. To be obtained by third-party evaluation via the Central Evaluation Committee.(2)If there is a period during which only EP-01 is placed, comparative evaluation will be conducted between the EEG measurement performance with EP-01 alone and with both EP-01 and intracranial electrodes in place, to ensure that there is no mutual interference.(3)To determine whether the waveforms detected by EP-01 are brain-generated EEG components, EEG changes with eyes open and closed will be observed. Evaluation will be conducted by a third party appointed by the Central Review Committee.(4)In the case of intracranial electrodes placed bilaterally, the percentage of agreement on lateralization of the epileptic focus between EP-01 EEG with noninvasive findings and findings from bilateral intracranial electrode EEG with noninvasive findings will be compared.(5)In the case of intracranial electrodes placed bilaterally, the percentage of agreement on lateralization of the epileptic focus between EP-01 EEG without noninvasive findings and findings from bilateral intracranial electrode EEG without noninvasive findings will be compared.(6)Diagnostic performance for the lateralization of the epileptic focus by EP-01 (percentage agreement with the results of diagnosis by intracranial electrodes with noninvasive findings) with noninvasive findings as evaluated by the primary investigators.(7)Epilepsy surgery outcome will be evaluated by the International League Against Epilepsy (ILAE) seizure outcome classification 1 year after focal resection.(8)Success rate of EP-01 implantation, calculated as the number of EP-01s implanted immediately after implantation/ number of microcatheters implanted x 100. In addition, whether the EP-01 has migrated from the target vessel will be evaluated immediately before removal.(9)Safety evaluations:aSeverity and temporal characteristics of adverse events (including medical procedures for implantation and removal of EP-01) and adverse events judged from imaging studies, etc., attributable to the study device (e.g., hemorrhage, midline shift, CSF leakage) (Each Primary Investigator evaluate whether the adverse events are attributable to EP-01 or invasive electrodes and ultimately compare which device is responsible for the adverse events)bIncidence and timing of adverse events (period of occurrence: from the start of use of the study device to the end of the post-observation period, including the start of use of the study device and the end of the post-observation period)cAssociations with all study devices (EP-01 body and EP-01 accessories), medical procedures for EP-01 implantation and removal, and other devices used in the study, judged by extent, severity, treatment, and outcome(10)Other evaluations:aFailure of EP-01 (EP-01 itself and EP-01 accessories)bOther failures of investigational devices (EX-01 extension wire/electroencephalograph)

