#### 2.2.3 *Follow-up.*

The EP-01 main unit is to stay implanted for up to 2 weeks (plus up to 3 days allowance) and then be removed. Intracranial electrodes will be removed according to clinical judgment and may be removed at the same time as the EP-01 unit. A follow-up period of 1 year will be conducted to evaluate the seizure-free rate after focal resection using data obtained from the EP-01 unit.

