#### 2.3.4 *Adverse events.*

An adverse event will be deemed as any unfavorable sign, symptom, or illness (including abnormal changes in laboratory values) observed during the study examination and post-observation periods after use of the EP-01 (main unit and accessories) or other investigational device (EX-01 Extension Wire/EEG 1200 Series Neurofax Electroencephalograph). Adverse events are also defined to include abnormal fluctuations in clinical laboratory values observed during the investigational testing and post-observation periods after use of the EEG1200 Series Neurofax, regardless of the causal relationship to the investigational device. If an adverse event is observed, the investigator shall take appropriate measures. In addition, regardless of the presence or absence of a causal relationship with the investigational device, follow-up investigations shall be conducted until, in principle, the event normalizes or recovers to a level where it is no longer considered an adverse event. If an irreversible adverse event is observed due to an organic disorder, follow-up investigations should be conducted until the symptoms are stabilized or fixed. Symptoms within the range expected for the primary disease will not be treated as adverse events. If focal epilepsy resection is performed during the study period, symptoms resulting from this procedure will not be treated as an adverse event. The numbers of adverse events, adverse events attributable to the study device, serious adverse events, and serious adverse events attributable to the study device will be tabulated in terms of the number of occurrences, number of cases, and percentage of cases with adverse events.

Safety assessments will also involve the operation of the implanted device. In this study, “failure” is defined as any malfunction of the investigational device, adverse effect of the investigational device on the human body, damage, malfunction, or other general unwellness, whether due to manufacturing, delivery, storage, or use.

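### Adverse-event recording stops one week after EP-01 removal, so intracranial electrodes that stay in longer can be under-observed in the planned comparison of which device caused harm

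*Protocol article*

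**What the plan says.** - **Sufficiency of the week.** Section 1.3, repeated in the Fig 1 legend: "The post-observation period (1 week) is judged as sufficient for monitoring potential adverse events associated with endovascular and intracranial implantation of electrodes."
- **Start of the week.** Abstract, Methods and analysis: "A post-observation period of one week will follow device removal to assess potential adverse events." The Fig 1 legend confirms the anchor. For a subject stopped during post-observation, "the tests specified one week after removal of the test device will be carried out as much as possible", and the trial then ends. The test device is EP-01.
- **Collection window.** Secondary endpoint 9b (Section 2.1.5) sets it "from the start of use of the study device to the end of the post-observation period". Section 2.3.4 defines adverse events as those "observed during the study examination and post-observation periods after use of the EP-01 (main unit and accessories) or other investigational device". Intracranial electrodes are not among the devices named there.
- **EP-01 dwell.** The Fig 1 legend has EP-01 in place until a seizure occurs or for at most 14 days, with a 3-day allowance.
- **Intracranial dwell.** Section 2.2.3: "Intracranial electrodes will be removed according to clinical judgment and may be removed at the same time as the EP-01 unit." No maximum is given. Section 2.1.3 places these electrodes after EP-01.
- **Use of the data.** Under endpoint 9a, investigators attribute each event to EP-01 or to the invasive electrodes "and [...]" then, in the protocol's words, "ultimately compare which device is responsible for the adverse events".

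**The concern.** The clock that ends adverse-event collection belongs to one device, while the comparison involves two. Every EP-01 is followed from insertion to 7 days after its own removal. An intracranial electrode has that follow-up only if it comes out no later than EP-01. Otherwise part of its post-removal week falls outside the window, and with a long enough lag so do its removal and its last days of dwell.

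Two things are at stake. The 9a comparison could set a fully observed device against a partly observed one, and no later analysis can recover events that were never collected. The statement that one week suffices for intracranial electrodes would also describe something the design does not secure.

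**Working it through.** The plan gives no figure for this point beyond the 14 (+3) day maximum for EP-01 and the one-week post-observation period, so there is no stated result to reproduce. The sample size plays no part.

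**Inputs**
- D = day of EP-01 removal, at most 14 (+3) (Fig 1 legend).
- Window closes on day D + 7 (Abstract; Fig 1 legend; endpoint 9b).
- k = days from EP-01 removal to intracranial removal. Not in the documents, so assumed over a range.
- Standard for adequate follow-up: 7 days after removal, taken from Section 1.3.
- Intracranial electrodes assumed in place from about day 0. They follow EP-01 insertion, so implantation itself ordinarily falls inside the window.

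**Formulas, for k ≥ 0**
- Post-removal days observed = max(0, 7 − k).
- Dwell days lost = max(0, k − 7).
- Total days lost = min(k, 7) + max(0, k − 7) = k.
- Share of dwell plus 7 days observed = (D + 7) / (D + k + 7).
- For EP-01 the share is always (D + 7) / (D + 7) = 100%.

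**Intracranial coverage by lag**

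| k (assumed) | Post-removal days observed | Dwell days lost | Share, D = 3 | Share, D = 14 |
|---|---|---|---|---|
| 0 | 7 of 7 | 0 | 10/10 = 100% | 21/21 = 100% |
| 3 | 4 of 7 | 0 | 10/13 = 77% | 21/24 = 88% |
| 7 | 0 of 7 | 0 | 10/17 = 59% | 21/28 = 75% |
| 11 | 0 of 7 | 4 | 10/21 = 48% | 21/32 = 66% |
| 14 | 0 of 7 | 7 | 10/24 = 42% | 21/35 = 60% |

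At k = 7 the intracranial removal falls on the last day of the window; above 7 it falls outside. If the intracranial electrodes come out before EP-01, there is no shortfall. For a given lag the share lost is larger when a seizure comes early, because the window then closes early.

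**Is a positive k plausible on the text?** Section 2.2.3 permits it. Section 1.1 names functional mapping as a main purpose of subdural electrodes and says EP-01 cannot practically serve it, so the intracranial electrodes have a use that need not end with EP-01 recording. The documents do not say how often, or for how long, they outlast EP-01.

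**Does any other passage close the gap?** Section 2.3.4 follows events until they normalise or stabilise, but this concerns events already observed and does not capture new ones after the window. The scheduled CT scans in Section 2.3.3 look for events from the EP-01 implantation site and end 7 days after removal. Nothing extends collection to or past intracranial removal.

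**Direction.** Unrecorded late intracranial events lower the intracranial count and leave the EP-01 count unchanged. EP-01 then looks relatively worse.

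**The case against.** The strongest reply has five parts.

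1. *The shortfall may never arise.* Same-time removal is expressly allowed. Section 2.1.3 makes special provision for therapies used at intracranial removal, and for resection before post-observation ends, which suggests that removal within the window is often expected. This stands as a limit on size. It is not a guarantee.
2. *Endpoint 9a is mainly attribution.* It states no rate, denominator or test, and the tabulation in Section 2.3.4 covers all events and those attributable to the study device. Attributing events seen during EP-01 exposure needs full EP-01 coverage, which exists. This largely stands, but 9a does go on to announce a comparison between devices.
3. *The sufficiency statement speaks of implantation*, which ordinarily falls inside the window. This is fair for the procedure itself. However, the statement justifies a period that begins only after removal, so it cannot be confined to the day of insertion.
4. *Longer recording without scans still leaves events judged on imaging unequally ascertained*, and a longer window may overlap with resection, whose symptoms are not counted as adverse events. This stands, and the fix has to deal with it.
5. *The article is condensed and the schedule figure is not shown.* The full protocol may set windows per device. That is possible, but the article itself states the window, the removal rule, the comparison and the sufficiency judgment, and these do not fit together.

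A reader might infer that the gap flatters EP-01 and so props up the less-invasive claim. The direction is the opposite. A reader might also infer that about half of the intracranial risk period goes unobserved. That figure (11 of 21 days, 52%) needs EP-01 out on day 3 and intracranial electrodes out on day 14, and both dates are assumptions.

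**Conclusion.** The point holds in a conditional form. By the protocol's one-week standard EP-01 is always fully observed, while intracranial electrodes removed k days later lose k days of observation. Post-removal days go first; the removal and k − 7 dwell days follow once k exceeds 7. The loss is zero for simultaneous or earlier removal. Since k is unknown, the documents support no overall figure for this trial and no statement that intracranial harms will be systematically under-counted.

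The 9a comparison can therefore under-count intracranial events, with a bias against EP-01, and the sufficiency statement in Section 1.3 and the Fig 1 legend is not guaranteed for intracranial electrodes. The result assumes that the article's window and removal rule are those of the full protocol. The consequence is confined to one part of one secondary safety endpoint.

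**What to change.** Record the insertion and removal dates of the intracranial electrodes in every participant. Then do one of the following.

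- **(a) Extend recording.** Collect adverse events to 7 days after the later of the two removals. The window then closes on day D + k + 7 for k ≥ 0, and both devices have at least 7 post-removal days. Report clinically detected events separately from those found on scheduled CT, which stays tied to EP-01 removal, and censor at resection. The cost is a few more days of adverse-event recording; no scan is added.
- **(b) Keep the window.** Limit the 9a comparison to the common period when both devices are in place and observed, and narrow the sufficiency statement in Section 1.3 and the Fig 1 legend to EP-01. The cost is a narrower comparison, which says nothing about harms at or after intracranial removal.

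Either way, Section 1.3, the Fig 1 legend, endpoints 9a and 9b, and Section 2.2.3 should be reconciled. Neither option changes the sample size, and no removal time is proposed for either device.
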